### Recruitment, consent and data collection

For the purpose of this study, all GPs practicing in the Nijmegen region are invited with a letter, in which the aim and procedure of the study are clarified. Furthermore, the advantages and disadvantages of participating are mentioned and contact information for advice from an independent physician is given. The researcher contacts the GPs several days after receipt of the letter. When more information is needed, the researcher visits the GP to inform him/her more extensively about the trial. When a GP refuses to participate, the researcher will document the arguments for non-respondent analysis. Inclusion starts at April 1 2011 and runs to October 1 2012.

When the patient and the family caregiver decide to join the study, they sign the informed consent form during a one-hour home visit by the researcher. After informed consent, the patient and the family caregiver will first complete the baseline measurement. The baseline measurement consists of several demographic questions and four short questionnaires for the patient. The four questionnaires (ESAS, PNPC-sv, HADS and NCQ) will be completed at home every four weeks during the study participation. The ESAS will be completed every week, as symptom burden is our primary outcome. The family caregiver completes a questionnaire on self-perceived pressure from informal care (EDIZ) at baseline and every two weeks. At time points where there is no home visit, the ESAS and EDIZ will be returned in a stamped envelope. The family caregiver receives a mobile phone text message as a reminder to fill in and post the questionnaires. The flowchart of the inclusion is described in Figure 1.

**Figure 1 F1:**
[figure not shown]
**Flowchart of the inclusion**.

### Outcome measures

#### Primary outcome

The symptom burden experienced by the patient, using the Edmonton Symptom Assessment System (ESAS) and the Hospital Anxiety and Depression Scale (HADS).

#### Secondary outcomes

1. The number of hospital admissions, which will be obtained from the patient's file.

2. The experienced problems and needs for palliative care (PNPC-sv; Problems and Needs in Palliative Care).

3. Patient and caregiver satisfaction with the teleconsultation (PSQ; Patient Satisfaction Questionnaire).

4. The experienced continuity of medical care in the last phase of life (Nijmegen Continuity Questionnaire; NCQ).

5. The experienced burden of the family caregiver (EDIZ; self-perceived pressure from informal care).

#### Other study outcomes

1. We will ask for some demographic information, such as age, marital status, number of children and living situation.

2. After the period of study inclusion (from the GPs patient record):

• Number of contacts by telephone with the GP practice

• Number of home visits by the GP

• Number of contacts with the GPs out of hours service

• Number of patients with complex interventions (such as palliative sedation)

• Number of and indications for hospital admissions

• Date and place of death

### Measurement instruments

The vulnerable condition of the patients was an important point of departure in the selection of the questionnaires. Important issues considered were length of the questionnaire, difficulty, the number of questionnaires and the time points of measurement. When it is impossible for the patient to complete the questionnaires independently, the informal caregiver is allowed to assist the patient. Table 1 gives an overview of the questionnaires used in the study.

**Table 1 T1:** Questionnaires used in the study

**Patient questionnaires**
Administered at baseline
• Basic demographic information (7 questions)
Administered at baseline and every week
• **ESAS **(Edmonton Symptom Assessment System)
- 10 items on symptom assessment
Administered at baseline and every four weeks
• **PNPC-sv **(Problems and Needs in Palliative Care - short version)
- 33 questions on experienced problems and needs for care
• **HADS **(Hospital Anxiety and Depression Scale)
- 14 items on anxiety (7 items) and depression (7 items)
• **NCQ **(Nijmegen Continuity Questionnaire)
- 28 items within 3 subscales on continuity of care
**Family caregiver questionnaire**
Administered at baseline and every two weeks
• **EDIZ **(one dimensional assessment of care burden)
- 9 items on the experienced burden from informal care
**Patient, GP and a member of the palliative consultation team**
Administered after the first two teleconsultations
• **PSQ **(Patient Satisfaction Questionnaire)
- 5 questions on satisfaction with the teleconsultation

#### Primary outcome

The ESAS is an easy to complete questionnaire developed for use in daily symptom assessment of palliative care patients. The patient rates the presence and severity of the following nine symptoms common in cancer patients: pain, activity, nausea, depression, anxiety, drowsiness, appetite, sense of well-being and shortness of breath. An optional tenth symptom can be added by the patient [33]. The items are rated on 0-10 visual numerical scales (with 10 being the worst imaginable intensity of a symptom). The ESAS is widely used and proven to be reliable [34,35].

The HADS is a 14-item self-report screening scale that was originally developed to indicate the possible presence of anxiety and depressive states in the setting of a medical non-psychiatric out-patient clinic. It contains two 7-item subscales on anxiety and depression. Each item scores on a 4-point Likert scale. The questionnaire assesses symptoms over the preceding week [36]. Psychometric properties of the HADS were assessed in six different groups of Dutch subjects (*N *= 6165). Homogeneity and test-retest reliability of the total scale and the subscales were considered adequate. The dimensional structure and reliability of the HADS is considered to be stable across medical settings and age groups [37].

#### Secondary outcomes

The PNPC is a self-reporting questionnaire for patients covering all dimensions of palliative care to investigate their problems and (unmet) palliative care needs. Experienced problems and needs for care are addressed separately, because patients could have had adequate assistance despite enduring symptom suffering. The original questionnaire with its 90 items has shown validity and reliability, but is not always practical for palliative patients. Therefore, a short version of 33 items has been developed and validated. This PNPC- short version was tested on 94 patients with metastatic cancer and has demonstrated construct validity. The dimension reliability was satisfactory, although two domains were less coherent [38].

The PSQ is a 5-item visual-analogue screening tool to measure patients' satisfaction, as well as doctor's satisfaction, following the consultation [39]. The questionnaire is developed and tested in the home situation in the Netherlands. Physician satisfaction turned out to be substantially lower than patient satisfaction, both at item level and at overall satisfaction level [39]. This finding is consistent with other patient satisfaction studies [40,41]. The PSQ is a short and easy to fill in questionnaire compared to many other patient satisfaction questionnaires and is therefore a very suitable instrument for the vulnerable patients participating in this study. The questionnaire will be completed by the patient, a member of the palliative consultation team and the GP following the first two teleconsultations.

The NCQ is developed and validated by the Radboud University Nijmegen Medical Centre (Department of Primary and Community Care). The questionnaire measures the patients' experienced continuity of care across primary and secondary care settings and consists of 3 subscales: 'Personal or relational continuity: care provider knows me' (5 items), 'Personal continuity: care provider shows commitment' (3 items) and 'Team/cross-boundary continuity' (4 items). Items are scored on a 5-point Likert scale, with an additional option to choose '?' ('do not know'). The NCQ was tested on 268 patients with a chronic disease and proved to be a reliable and valid instrument with good discriminant abilities [Uijen AA, Schellevis FG, Mokkink HGA, van Weel C, van den Bosch WJHM, Schers HJ: Measuring continuity from the patient perspective: psychometric properties of the Nijmegen Continuity Questionnaire (NCQ), submitted]. In this study, only the domains on the experienced quality of the relation between GP and specialist and the confidence in the GP and in the specialist are being used. Publications on the development of the questionnaire and the examination of the reliability and validity have been submitted to a journal and are available on request.

The EDIZ is a 5-point Likert scale screening questionnaire with 9 subjects to measure the self-perceived burden from informal care. This burden is expressed in thoughts (e.g. 'the situation of my.... is constantly on my mind') as well as in his/her interaction with the social environment (e.g. 'it's not easy to combine the responsibility for my ... with the responsibility for my work/family'). The EDIZ is a validated instrument [42].

### Sample size calculation

The null hypothesis of this cluster randomized trial is that there are no significant differences in symptom distress between palliative patients at home with and without a telemedicine-computer for videoconference. Symptom distress will be measured by the Edmonton Symptom Assessment Scale (ESAS). The ESAS is a 0 to 10 numeric scale (0 = best, 10 = worst) to rate severity of 10 symptoms. The sum of all 10 scales makes the Total Distress score (max.100). Based on a study of Follwell et al. [43] we determined a Total Distress score of 8 as the minimum clinically important difference for the power calculation. Without a cluster-effect and without repeated measures, we would need 80 patients per condition, assuming an α of .05 and a power of 80% (calculated with nQuery advisor 4.0). However, there is a cluster-effect and there are repeated measures that we corrected for.

To correct for clustering, we multiplied the abovementioned sample size with the design factor (1+(n-1)ICC), where n is the number of patients and ICC the intra cluster correlation. Assuming 3 enrolled patients per GP and an ICC of 0,1 (based on Knox & Chondros [44]), the design factor for clustering is 1,2.

To correct for repeated measures and baseline measurement, we also multiplied the sample size with the design factor ((1+(k-1)ρ)/k- ρ_0_^2^). In this formula, k is the number of repeated measures, ρ is the (mean) correlation between pairs of post-tests and ρ_0 _is the (mean) correlation between a post-test and the baseline measurement. Here, k = 13, and we state ρ = 0,45 [34] and ρ_0 _= 0,35. The design factor for repeated measures is therefore 0,37.

That makes the total required sample size 80 × 1,2 × 0,37 = 36 patients per condition. Taking into account an early drop-out of patients, we aim to include 50 patients per condition. This calculation is based on Follwell et al. [43], who considered a drop-out of 30% within an inclusion period of 1 month. Because the inclusion period in our study is longer (estimated life-expectancy of approximately 3 months at inclusion), we chose a higher drop-out percentage (39%).

Put briefly, a sample size of 100 patients (α = .05, power = 80%) is required to detect differences in change of symptom distress between the intervention group and the control group.

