### Statistical analysis

The data will be stored and analyzed in the Radboud University Nijmegen Medical Centre using the Statistical Package for the Social Sciences (SPSS version 16.0, SPSS inc., Chicago, Illinois, USA). Data cleaning will be performed via SPSS syntax operations. All statistical tests will be done two-tailed with 95% confidence intervals.

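### The 39% drop-out allowance does not fit the plan's own numbers: enrolling 50 to keep 36 per condition covers about 28% loss

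*Protocol article*

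**What the plan says.** All the figures are in the protocol article, under Sample size calculation.

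- The starting point is a two-group comparison: "we would need 80 patients per condition", "assuming an α of .05 and a power of 80"%, for a difference of 8 points on the ESAS Total Distress score.
- After the factors for clustering and for repeated measures, the requirement is "80 × 1,2 × 0,37 = 36 patients per condition".
- For early drop-out this is raised: "we aim to include 50 patients per condition".
- The benchmark is the source study, "who considered a drop-out of 30% within an inclusion period of 1 month". Because follow-up is longer in this trial, "we chose a higher drop-out percentage (39"%).
- The section closes by giving 100 patients as the number needed for 80% power at α = .05.

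The Statistical analysis section adds that tests are two-tailed. The Multivariate analysis section names linear mixed models as the method.

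**The concern.** A drop-out percentage is naturally read as the share of enrolled patients who are lost. The text supports that reading, because it compares 39% directly with a drop-out of 30% in another study. On that reading, the enrolment number is the required number divided by (1 − drop-out). Going from 36 to 50 does not correspond to 39% on this scale.

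Two things are at stake. First, the section offers 39% drop-out, 100 patients and 80% power as a consistent set, and they are not one under the section's own method of finding a requirement and then adding an allowance for losses. Second, the reader is told that the allowance is more cautious than the source study's 30%, whereas 50 per condition covers slightly less than 30%. This is the only sample size justification shown, and it concerns the primary outcome in a population where early loss is expected.

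**Working it through.** **Inputs** (Sample size calculation, unless noted): 80 per condition before adjustment; 3 patients per GP and ICC 0.1; k = 13, ρ = 0.45, ρ₀ = 0.35; 36 required and 50 enrolled per condition; drop-out 39%, source study 30%; α = 0.05, two-sided (Statistical analysis); power 80%.

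**Step 1: reproduce the 36.**
- Clustering factor: 1 + (3 − 1) × 0.1 = 1.2, as stated.
- Repeated-measures factor: (1 + 12 × 0.45)/13 − 0.35² = 0.3698, stated as 0.37.
- Requirement: 80 × 1.2 × 0.37 = 35.5, rounded up to 36, as stated.

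**Step 2: reproduce the 50.**
- As a mark-up, n × (1 + d): 36 × 1.39 = 50.04. This gives the printed figure.
- As a share of those enrolled, n/(1 − d): 36/0.61 = 59.02. This does not.
- Rounding does not explain the gap: from 35.5 the two routes give 49.4 and 58.2.

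The article does not write out 36 × 1.39. That this was the route is inferred from the fit.

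**Step 3: the loss that 50 can absorb.**
- 1 − 36/50 = 28%; from the unrounded figure, 1 − 35.5/50 = 29%.
- Even 30% would need 36/0.70 = 51.4 (50.7 from 35.5), slightly more than 50.

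**Step 4: the enrolment that 39% would need.**
- 59 × 0.61 = 35.99 and 60 × 0.61 = 36.6, so 59 to 60 per condition, or 118 to 120 in total.

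**Step 5: power if 39% are lost and contribute nothing after baseline.**
- Remaining per condition: 50 × 0.61 = 30.5.
- Power = Φ((1.96 + 0.84) × √(remaining/required) − 1.96).
- Against 36: 73.2%. Against 35.5: 73.8%.

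The SD is not stated in the article and is not needed here, because the result depends only on the ratio of remaining to required patients. The clustering factor is held at 1.2.

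**The case against.** The strongest reply concerns the power figure. The article states no rule that a patient who drops out contributes nothing. ESAS is collected weekly, and a linear mixed model keeps patients with partial follow-up. By the plan's own repeated-measures formula, one post-test gives a factor of 1 − 0.35² = 0.8775, so a drop-out with a single post-baseline form carries 0.3698/0.8775 = 0.42 of a completer's information. If all 19.5 drop-outs per condition returned one form, the effective number would be 30.5 + 19.5 × 0.42 = 38.7, above 36, with power of about 83%. About two thirds of them doing so would restore 36 (30.5 + 13 × 0.42 ≈ 36).

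The clustering factor would also fall with fewer retained patients per GP. With 3 × 0.61 = 1.83 on average it is about 1.08, or about 1.12 (1 + 2 × 0.61 × 0.1) if losses are random and unequal across GPs. The requirement then drops to 32 to 33, and power with 30.5 remaining is about 77 to 78%, even with no data from drop-outs.

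Both arguments stand, and they make 73 to 74% a worst case. They do not remove the inconsistency, because the section claims neither credit: it computes 36 and then adds an allowance for losses. The first argument also assumes a treatment effect that is constant over the weeks, as the plan's formula does. Incomplete follow-up does not act only in the plan's favour either: the 0.37 assumes 13 post-tests per patient in people with a life expectancy of at most 3 months.

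A second reply is that the source study's 30% may itself have been a mark-up, which would make 39% higher on the same scale. This cannot be checked from the document. The wording, a drop-out of 30% within a month, points to a share of enrolled patients.

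**Conclusion.** Wrong as written. With 36 required and 50 enrolled per condition, the allowance is 28% (29% unrounded), not 39%, and it falls just short of the 30% it is said to exceed. The comparison with 30% assumes that the source figure is a share of enrolled patients. A true 39% allowance needs 59 to 60 per condition.

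The consequence for power is conditional. It is about 73 to 74% at 39% drop-out if those patients provide no post-baseline data and the clustering factor stays at 1.2. Otherwise the shortfall from 80% is smaller or absent.

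A reader might infer more than this:
- **That the trial is underpowered or must recruit 118 to 120 patients.** The document does not support that, because the planned analysis uses partial follow-up and the timing of losses is unknown.
- **That 30% in one month can be compounded over three months to show a much larger loss.** That needs a constant monthly rate, which the article does not state, so no such figure is used here.

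**What to change.** Correct the drop-out sentence in the Sample size calculation section, and leave the target of 100 unchanged. Choose one of two forms:

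1. State that 50 per condition retains the required 36 with up to 28% drop-out, and remove the statement that the allowance is higher than the source study's 30%.
2. Keep 39%, and state that 50 per condition then leaves about 30 patients per condition and power of about 73 to 74% for a difference of 8 points if drop-outs contribute no post-baseline data. If the sponsor wishes to credit partial follow-up in the mixed model, that credit and its assumptions should be written out. The comparison with 30% may then stay.

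The closing statement of 100 patients and 80% power should carry the same condition as the form chosen. The cost is wording only, with a slightly less favourable stated allowance or power. No procedure, analysis or recruitment target changes.

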### Randomization

Participating GPs will be randomly assigned to the intervention group or to the control group. Due to clustering of GPs, all subsequently referred patients will be in the same study group. A block design with different length of blocks (4 and 6) will be used to give an equal balance between groups. An independent researcher will generate and store the randomization code.

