### Study population

On the moment of inclusion, the patient's GP acts as the coordinator of medical care, and patients reside at their homes. Besides the place of residence, the inclusion criteria are:

- Dutch-speaking patients, aged 18 years or older, with a progressive oncological disease,

- a score of ≤ 60 on the Karnofsky Performance Scale (assessed by the GP),

- a life expectancy of ≤ 3 months.

Patients unable to give informed consent and patients with an active psychotic disorder or a serious cognitive disorder are not eligible for inclusion.

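### The 39% drop-out allowance covers about three months and the cited 30% covers one, so on a common time scale it is lower, and the step from 36 to 50 patients per condition is not supported

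*Protocol article*

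**What the plan says.** The Sample size calculation section of the protocol article starts from a difference of 8 points on the ESAS Total Distress score and states that "we would need 80 patients per condition, assuming an α of .05 and a power of 80"% before any correction. A factor of 1.2 for clustering and 0.37 for 13 repeated measures with a baseline bring this to 36 per condition. Enrolment is then set at 50 per condition to cover early drop-out.

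The drop-out figure rests on one cited study, "who considered a drop-out of 30% within an inclusion period of 1 month". The plan notes that its own period is longer, about three months, and for that reason "we chose a higher drop-out percentage (39"%). No further derivation is given. The Study population section makes "a life expectancy of ≤ 3 months" an entry criterion.

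**The concern.** The plan itself names the longer follow-up as its reason for adjusting the source's figure. Three times the duration adds 9 percentage points. The two percentages refer to different lengths of time, so calling one higher than the other says nothing about the rate of loss. Put on the same scale, the allowance assumes that these patients leave more slowly than the source's patients did, and nothing in the text explains why. The entry criterion and the Ethical considerations section, which expects patients' condition to worsen towards the end, give no support for slower loss later on.

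At stake is the written basis for the target of 100 patients and the 80% power statement. The route from 36 to 50 makes sense only if about 36 per condition remain after losses.

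**Working it through.** **Inputs.** From Sample size calculation: 80 per condition uncorrected, α 0.05, power 80%, 3 patients per GP, ICC 0.1, k = 13, ρ = 0.45, ρ₀ = 0.35, 30% loss in one month at the source, 39% here, about three months of follow-up, 50 enrolled. From Statistical analysis: two-sided tests.

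**The plan's 36.**
- Cluster factor: 1 + (3 − 1) × 0.1 = 1.2.
- Repeated-measures factor: (1 + 12 × 0.45)/13 − 0.35² = 0.3698.
- 80 × 1.2 × 0.3698 = 35.5, rounded up to 36. This reproduces.

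**The plan's 50.** 36 × 1.39 = 50.04 gives the stated figure. Retaining 36 after 39% loss would take 36/0.61 = 59.02, so 59 to 60. This is a separate error, noted here because it affects the comparisons below.

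**The rate on one time scale.**
- Average monthly loss implied by 39% over three months: 1 − 0.61^(1/3) = 15.2%, about half of 30%.
- If month 1 matches the source, what is left for months 2 and 3: 1 − √(0.61/0.70) = 6.6% per month.

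**What needs no projection.**
- At the cited rate, 50 × 0.70 = 35 remain after one month.
- Keeping 36 of 50 allows 1 − 36/50 = 28% loss over the whole follow-up, less than the source lost in one month.

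**Retention at three months, which does need an assumption after month 1.**

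| Assumption | Loss | Remaining of 50 |
|---|---|---|
| Plan's 39% | 39% | 50 × 0.61 = 30.5 |
| 30%, then 5% per month | 1 − 0.70 × 0.95² = 37% | 31.6 |
| 30%, then 20% per month | 1 − 0.70 × 0.80² = 55% | 22.4 |
| 30% every month | 1 − 0.70³ = 66% | 17.2 |

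**Power if only retained patients count.** With n such patients, the equivalent uncorrected number is n/(1.2 × 0.3698), and power = Φ(2.80 × √(that number/80) − 1.96).
- n = 36: 81%.
- n = 30.5: 74%.
- n = 17.15: 49%.

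**Power if partial data count.** A patient with k post-baseline scores carries information 1/((1 + (k − 1) × 0.45)/k − 0.1225). Average this over a constant weekly loss, with patients who give no score carrying none. Keep the factor 1.2, and assume ignorable loss, no other missed weeks and the same treatment difference each week.
- 39% loss: about 10.1 scores per patient, average information 2.43, equivalent number 50 × 2.43/1.2 = 101, power 88%.
- 66% loss: about 7.7 scores per patient, average information 2.16, equivalent number 50 × 2.16/1.2 = 90, power 84%.

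Both equivalents exceed the 80 required.

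**The case against.** As cumulative percentages, 39% is higher than 30%, and it is a planning assumption that no formula in the plan contradicts. The source may have lost patients mainly at the start, in which case slower later loss would be reasonable; 39% lies inside the 37% to 55% range above. This stands as a reason not to call 39% impossible. It does not supply the missing justification, because the plan gives duration as its only reason for adjusting.

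A reader might infer that the plan's own figures imply 66% loss, or that only 17 to 25 of 50 would remain. The documents do not support that. They give one rate, for one month. The 66% assumes that it continues unchanged; about 49% assumes that it halves to 15% after month 1 (1 − 0.70 × 0.85²); 50% assumes that the entry criterion is a median survival of three months. None of these is stated.

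Nor does the protocol say that 36 patients will be measured at week 13; it speaks of early drop-out. And the shortfall from 36 to 30.5 at the plan's own 39% comes from the conversion error, not from the rate. The fair comparator for the effect of a higher rate is therefore 30.5 patients and 74% power.

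The strongest objection is that Linear Mixed Models are planned (Multivariate analysis section) and use the scores of patients who leave. That stands, and it removes any claim that 50 enrolled is too few on this ground. It is conditional on ignorable loss, which is a demanding assumption when much of the loss is likely to be death or deterioration, and on few missed forms. It is also not the argument the plan makes: the factor 0.37 credits each of the 36 with all 13 scores.

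**Conclusion.** The concern holds in a limited form. The 39% is not a higher rate than the cited 30%: it averages about 15% per month, without explanation. The stated route from 36 to 50 already fails at one month on the cited rate, 35 against 36, with about two months of follow-up still to come.

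How far retention falls after that cannot be read from the documents. It is 30.5 of 50 at the plan's own 39%, about 32 to 22 if later loss is 5% to 20% per month, and 17 if 30% per month continues. The 49% power figure belongs to the last case with every score of departed patients discarded, which is not the planned analysis. Under the planned model, with the assumptions stated in the working, 50 enrolled gives about 84% to 88%.

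So the justification is wrong while the enrolled number may still be defensible on another basis. This should be corrected, but it does not show that the trial is too small.

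**What to change.** Rewrite the drop-out paragraph:

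1. Replace 39% with a loss assumption on the same time scale as the cited 30% per month, shown as a range and labelled as an assumption.
2. Replace the basis of 36 plus drop-out with the power of 50 enrolled per condition across that range under the planned mixed model. State that this assumes ignorable loss and give the allowance for missed scores. Put the retained-only figure beside it.
3. Correct the conversion of the percentage. If the text keeps 36 as a number to be retained, the divisor is one minus the loss: 36/0.61 gives 59 to 60 at 39%. Correcting the rate alone would not repair the calculation.

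The cost is one paragraph and a less favourable stated retention. No extra patients are needed if power is based on 50 enrolled as in step 2. If the sponsor instead insists on retaining 36, the target rises to 57 to 81 per condition for later loss of 5% to 20% per month (36/0.63175 and 36/0.448), and to 105 if 30% per month continues (36/0.343).
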